##### Personality traits

Personality traits are measured, among others, with the Ten-Item Personality Inventory (TIPI; [145, 146]), which is a brief measure of the Big-Five personality dimensions. The 10 items can be rated on a seven point Likert scale. The TIPI has shown low to moderate internal consistency and adequate validity among students [145, 146].

##### Positive mental health

Positive mental health, often referred to as mental well-being, is assessed using the nine-item Positive Mental Health scale (PMH-scale; [147]). The items can be rated on a nine point Likert scale. Based on a previous study on the psychometric properties of the PMH-scale in student, patient and general samples, the PMH-scale was found to be a reliable and valid instrument [147].

##### Psychopathology and maladaptive personality traits

The Minnesota Multiphasic Personality Inventory-2 Restructured Form (MMPI-2-RF; [148]) measures a wide range of psychopathology symptoms, personality characteristics, and behavioral proclivities. The MMPI-2-RF consists of 338 true-false items aggregating onto 51 individual scales. The psychometric properties of the MMPI-2-RF varied from inadequate to good among normative, outpatient, and inpatients samples, as documented in detail in the Technical Manual [149].

##### Readiness to change

Readiness to change is assessed by two subscales (contemplation and action) of the 24-item version of the University of Rhode Island Change Assessment (URICA; [150–152]). Both subscales are measured by six 5-point Likert scale items and have demonstrated good reliability across a diversity of studies (e.g., [153–155]).

##### Rigidity

Rigidity is measured by the Rigidity subscale of the Computerized Adaptive Test of Personality Disorder-Static Form (CAT-PD-SF; [156]). The Rigidity subscale contains 10 five point Likert scale items reflecting an unwillingness to consider alternative perspectives and inflexibility in values and beliefs. The subscale has demonstrated good reliability among community adults with current or a history of mental health treatment [156].

##### Social problems

By using the social problems list, derived from the Improving Access to Psychological Therapies (IAPT) program [157], social problems (e.g., financial problems, housing problem, and unemployment) are assessed in direct discussion with the patient.

##### Social support

The Multidimensional Scale of Perceived Social Support (MSPSS; [158]) is assessed to investigate perceived support from three sources: significant others, family, and friends. The MSPSS contains 12 items which can be rated on a seven point Likert scale. Psychometric properties of the MSPSS are satisfactory among psychiatric outpatients and BPD patients [159, 160]. In addition to the MSPSS, the research assistant rates the patient’s social network taking into account the size of the network and potential pathogenic influences.

##### Stigma of immutability

BPD has been associated to stigma of immutability [161]. We have developed five 7-point Likert scale items assessing the extent to which participants believe that BPD is resistant to treatment.

##### Trauma

The Traumatic Experience Checklist (TEC; [162]) is used to assess traumatic experiences, including emotional abuse, emotional neglect, sexual abuse, sexual harassment, physical abuse, and threat to life/ bizarre punishment/ intense pain. The TEC includes 30 descriptions of various traumatic experiences. The TEC has demonstrated favorable psychometric properties in Dutch psychiatric patients [162].

##### Verbal intelligence

The Dutch version of the National Adult Reading Test (DART; [163]) is used as a proxy for verbal intelligence. The DART is a reading test including 50 irregularly spelled words. Based on previous research, the DART yields an adequate estimation of verbal intelligence and has shown adequate psychometric properties across a variety of populations [164].

##### Other patient characteristics, collected using a self-report questionnaire

In addition to the questionnaires, participants fill out several questions developed by the authors about the willingness and ability to engage in a therapeutic relationship, perceived suitability of DBT and ST (treatment preference), and the absence or presence of an attachment figure in the past.

##### Other patient characteristics, collected using a questionnaire filled out by clinicians (intake questionnaire)

Clinicians responsible for the intake assessment will fill out the nine-item intake questionnaire for each participant, including questions about the willingness and ability to engage in a therapeutic relationship, the willingness and ability to examine the link between childhood history and present problems, high vs. low level borderline personality organization [165], the request for help, the degree to which a syndrome disorder might interfere with treatment response, and perceived suitability of DBT and ST. These questions have been formulated by the authors.

#### Mediators

Both treatments include non-specific (attachment and therapeutic alliance), BPD-treatment-generic (therapeutic environment characterized by genuineness, safety, and equality), and BPD-treatment-specific (ST: beliefs and schema modes; DBT: emotion regulation and skills use) mechanisms of change. The proposed mediators are repeatedly measured: at baseline, except for measures requiring information about the therapy (i.e., therapeutic environment, therapeutic alliance, and attachment styles with respect to the most important therapist and group members), and every six months after start of the treatment phase. In addition, a selection of the proposed mediators (i.e., selection of schema modes, skills use, beliefs, and therapeutic environment) are also collected every three months after start of the treatment phase, during the first two years.

##### Attachment

The Experience in Close Relationships-Relationship Structures Questionnaire (ECR-RS; [166]) is a brief version of the Experience in Close Relationships-Revised (ECR-R; [167]). The ECR-RS measures attachment patterns in different relational domains, such as relationships with parents and friends. The ECR-RS can also be adapted to measure a person’s general attachment style. In this study, three versions of the ECR-RS are used, measuring general attachment style and attachment styles with respect to two targets (i.e., most important therapist and group members). The ECR-RS contains nine items, assessing two attachment dimensions: attachment-related anxiety and avoidance. The items can be rated on a seven point Likert scale. The ECR-RS has shown adequate psychometric properties in a large web-based sample (*N* > 21.000), comparable to the ECR-R [166]. As experience with the treatment is required in order to be able to complete the questions about the most important therapist and group members, these questions will be filled out three weeks after start of the treatment phase.

##### Beliefs

Idiosyncratic dysfunctional beliefs were elicited with a semi-structured interview at baseline. Three to five idiosyncratic dysfunctional beliefs related to the self (e.g., “I am worthless”), others (e.g., “People always reject me”), and emotions (e.g., “Expressing emotions is a sign of weakness”) are formulated. Participants rate the degree to which they believe in each statement on a 100 mm VAS at baseline and at every subsequent assessment. This procedure has been used in previous research (e.g., [168, 169]). The VAS has found to be useful for assessing variations in intensity of beliefs in patients with a personality disorder [169]. In addition to the idiosyncratic dysfunctional beliefs, participants rate the credibility of one functional belief (“I consider myself a good person”) on a 100 mm VAS.

##### Emotion regulation

Emotion regulation is assessed by the Difficulties in Emotion Regulation Scale Short Form (DERS-SF; [170]), a brief version of the widely used DERS [171]. The DERS-SF measures non-acceptance of emotional responses, difficulties engaging in goal-directed behavior, impulse control difficulties, limited access to emotion regulation strategies, lack of emotional clarity, and lack of emotional awareness. The awareness subscale is excluded based on recommendations of among others Hallion et al. [172] and Bardeen et al. [173]. Lack of emotional awareness is assessed by the Awareness subscale of the Difficulties in Emotion Regulation Scale 18 (DERS-18; [174]). The DERS-SF, without the awareness subscale, consists of 15 items. The Awareness subscale of the DERS-18 is measured by three items. All items can be rated on a five point Likert scale. Both questionnaires have demonstrated good psychometric properties among outpatients [172].

##### Schema mode ratings

The Schema Mode Inventory (SMI; [175]) measures the extent to which 16 different (dysfunctional as well as functional) schema modes are endorsed. The SMI consists of 143 items that are scored on a six point Likert scale. Previous research using a sample of non-patients and patients with a syndrome disorder and/or personality disorder has demonstrated acceptable psychometric properties [176]. The five maladaptive schema modes that are central to BPD (i.e., vulnerable child, angry child, impulsive child, detached protector, and punitive parent; [101]) and one functional schema mode (i.e., healthy adult) are assessed every three months during the first two years.

##### Skills use

The 59-item Dialectical Behavior Therapy-Ways of Coping Checklist (DBT-WCCL; [177]) is an adaptation of the Revised Ways of Coping Checklist (RWCCL; [178]). The DBT-WCCL measures DBT skills use and maladaptive coping skills use over the previous month. All items are assessed using a four point Likert scale. The DBT-WCCL has shown adequate to excellent reliability and validity among BPD patients [177].

##### Therapeutic alliance

The therapeutic alliance is measured with the Working Alliance Inventory-Short (WAI-S; [179, 180]). The WAI-S consists of three subscales (agreement on goals, agreement on tasks, and bond between patient and therapist), each consisting of four items which can be scored on a five point Likert scale. Observed psychometric properties of the WAI-S were satisfactory in a patient sample [179, 181]. Since experience with the treatment is required in order to be able to complete the WAI-S, the WAI-S will be filled out three weeks after start of the treatment phase.

##### Therapeutic environment

Key characteristics of a promoting therapeutic environment (i.e., genuineness, safety, and equality) are assessed by 13 items formulated by ST experts ([name] and [name]) and rated on a 100 mm VAS. The items measure the extent to which the participant feels a) the individual therapist, group therapists, and group members are genuine with him/her; b) he or she can tell the individual therapist and group therapists everything; c) safe in the individual and group therapy; d) safe to show vulnerability and express negative feelings in the individual and group therapy; e) the individual and group therapists take personal responsibility for their mistakes; and f) the individual and group therapists see him/her as equal. Since experience with the treatment is required in order to be able to complete this questionnaire, this questionnaire will not be assessed at baseline.

#### Primary outcome

##### BPD severity

The primary outcome measure is the change in severity and frequency of the DSM-5 BPD manifestations between baseline until three-year follow-up, assessed with the total score of the Borderline Personality Disorder Severity Index version 5 (BPDSI-5; [182, 183]). The BPDSI-5 is a semi-structured interview consisting of 70 items rating the nine DSM-5 BPD criteria over the prior three months. All items are rated on a 11-point Likert scale (0 = never to 10 = daily), except for the subscale Identity Disturbance which is rated on a 5-point Likert Scale (0 = absent to 4 = dominant, clear, and well-defined) and multiplied by 2.5. The total score consists of the sum of the nine criteria scores and ranges from 0 to 90. The scores on the BPDSI-5 subscales provide information on the severity of each of the nine criteria. The BPDSI-5 is a modified version of the BPDSI-IV [182, 183] in which a few questions have been slightly reworded and exact frequency scores have been added in addition to the Likert scale. The BPDSI-IV has proven to be a reliable and valid measure among non-patients and (BPD) patients [182, 183]. Previous research has shown that a cut-off score of 15 differentiates between BPD patients and controls [183]. In addition, a score of 20 distinguishes BPD patients from non-BPD patients [183–185].

#### Secondary outcome measures

As accumulating evidence suggests that BPD severity and level of functioning are only loosely associated, attention will be paid to outcomes in different areas, including symptoms, functioning, and well-being. The outcome measures are administered at baseline and every six months after start of the treatment phase. In addition, patients’ ratings of experienced burden due to BPD manifestations and well-being are collected every three months after start of the treatment phase, during the first two years.

##### Costs

Costs, including healthcare costs, patient and family costs, and costs outside the healthcare sector, are measured using a retrospective cost interview especially designed for BPD patients [80]. Healthcare costs include visits to general practitioners, hospitals, crisis centers, psychologists and psychiatrists, use of medication, social work, paramedical care, and alternative treatments. Patient and family costs include informal care (i.e., care provided by the patient’s family, friends, or neighbors) and out of pocket costs (e.g., drugs, alcohol, excessive spending). Costs in other sectors include productivity losses from unpaid work (study and voluntary work) and paid work. Since it is difficult to distinguish between BPD-related costs and costs due to other psychological disorders [17], only a distinction will be made between costs due to psychological disorders and costs due to somatic diseases. The cost interview will be conducted by trained research assistants using a recall period of six months (baseline assessment), the number of weeks since randomization (assessment six months after start of the treatment phase), or the number of weeks since the previous assessment (assessments 12, 18, and 24 months after start of the treatment phase and both follow-up assessments).

Dutch guidelines [186, 187] will be used to determine total costs. Healthcare costs will be calculated by volumes of resource use multiplied by their corresponding unit costs, derived from Hakkaart-van Roijen et al. [186]. Prescribed medication costs will be determined based on national reference prices. Informal care costs will be computed by multiplying the number of hours the patient receives informal care by shadow prices [186]. Shadow prices will also be used to value lost productivity in study and voluntary work. Productivity losses from paid work will be valued according to the Human Capital Approach [188]. Out of pocket costs, such as alcohol and excessive spending, will be directly retrieved from the cost interview or, in case of over-the-counter medication, from the Dutch Pharmacotherapeutic Compass [186].

##### Demographics

General patient characteristics (e.g., age, ethnicity, marital status, educational level, employment status) will be collected using a semi-structured demographic interview. During this interview, additional patient characteristics such as treatment history, request for help, medication use, substance use, and duration of BPD manifestations will be recorded. For an overview of all characteristics, see Additional file 4.

##### Experienced burden due to BPD

Patient’s self-reported experienced burden of BPD manifestations are measured using the Ultrashort BPD Checklist, a shortened version of the validated BPD Checklist [189]. The Ultrashort BPD Checklist consists of nine to 11 5-point Likert scale items (the number of items will be based on the upcoming validation study), each related to a specific DSM-5 BPD criterion. Based on an initial psychometric evaluation, the Ultrashort BPD Checklist showed good to excellent psychometric properties in a sample with BPD and cluster C patients, patients with a syndrome disorder, and non-patients, similar to the BPD Checklist [189].

##### General psychopathological symptoms

The Brief Symptom Inventory (BSI; [190, 191]) is a self-report instrument measuring general psychiatric symptoms at the time of assessment. The BSI is a short version of the Symptom-Check-List (SCL-90-R) and contains 53 items assessing nine symptom dimensions: somatization, obsession-compulsion, interpersonal sensitivity, depression, anxiety, hostility, phobic anxiety, paranoid ideation, and psychoticism. All items are assessed using a five point Likert scale. Previous research in Dutch community and patient samples has demonstrated good reliability and validity [191, 192].

##### Global functioning and impairment

Global functioning and impairment is assessed by the 36-item World Health Organization Disability Assessment Schedule 2.0 (WHODAS 2.0) interview version [193]. The WHODAS 2.0 is a general measure to assess disability in six major life domains (cognition, mobility, self-care, getting along, life activities, and participation). For each item, participants have to report how much difficulty they experienced in the last 30 days. The six domain scores and overall functioning score have shown good psychometric properties in a general population sample as well as a patient sample [193].

##### Quality of life

Generic quality of life is assessed using the 5-level EuroQol 5D version (EQ-5D-5L; [194]). The questionnaire measures five health state dimensions (mobility, self-care, usual activities, pain/discomfort, and anxiety/depression). Each dimension is divided into five severity levels: no problem, slight problems, moderate problems, severe problems, and extreme problems. The profiles from the five health state dimensions are assigned a value based on the Dutch social tariffs to generate health utilities [195]. These utilities will be used to calculate Quality Adjusted Life Years (QALYs) by multiplying the change in utility values between assessments by the length of the period between assessments. In addition to the five health state dimensions, the EQ-5D-5L contains a VAS item which records the patient’s self-reported health status ranging from 0 (worst health you can imagine) to 100 (best health you can imagine). The EQ-5D-5L has shown to be a reliable and valid measure among different patient groups in different countries [196].

As a complement to the EQ-5D-5L, the Mental Health Quality of Life seven-dimensional Questionnaire (MHQoL-7D; [197]) will be administered. The MHQoL-7D is a recently developed instrument to assess quality of life specifically in people with mental health problems. The MHQoL-7D consists of seven quality of life domains (self-image, independence, mood, relationships, daily activities, physical health, and hope) and a VAS item which records the patient’s self-reported psychological well-being. A study into the psychometric properties of the MHQoL-7D is currently running. The MHQoL-7D will only be included in the analysis if it is demonstrated to be a psychometrically sound instrument and Dutch social tariffs are available.

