### Procedure and assessments

Patients with BPD or suspected of BPD are invited to the screening process by the research assistant or intake staff member. After providing written informed consent, patients are assessed for eligibility to participate in the study based on the inclusion and exclusion criteria. First, to assess DSM-5 syndrome disorders, the SCID-5-S is administered. The SCID-5-PD will also be administered in case the SCID-5-PD is not part of the standard intake procedure of the mental healthcare center. Second, the BPDSI-5 and a screening interview to assess the motivation and availability of the patient are conducted. A simple “yes” answer to the questions posed by the interviewer (e.g., “Are you motivated and available for treatment, including individual and group sessions?”) is not sufficient. Patients need to elaborate on their answers and follow-up questions are asked if needed. Patients who are eligible for participation will be invited for the baseline assessment, including interviews and computer-based self-report questionnaires, and intake staff members will fill out a questionnaire (i.e., intake questionnaire; see the Measures section) about these patients. After completing the baseline assessment, patients will be randomized as soon as treatment slots become available. Patients will be informed that they have been allocated to one of the treatment conditions, but the name of the treatment will not be communicated to the patient until the first treatment session. If patients cannot be randomized within several months after completing the baseline assessment because of unavailability of treatment slots, the BPDSI-5 will be re-assessed after three months and the BPDSI-5 and cost interview will be re-assessed after six months.

After the treatment phase has started, patients are reassessed every six months during the two years of treatment. These assessments are a combination of interviews and computer-based self-report questionnaires. In addition, a selection of measures are also assessed every three months, by computer-based self-report questionnaires. After end of the treatment, two follow-up assessments (six and 12 months after end of the treatment) will be administered. An overview of the measures is presented in Table 1. Candidate predictors of (differential) treatment response that are assessed only once at baseline are not included in Table 1. These measures can be found in the Measures section.

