#### Cost-effectiveness

The cost-effectiveness evaluation will be performed from a societal perspective and includes a cost-effectiveness analysis (CEA) and cost-utility analysis (CUA). The primary clinical outcome for the CEA will be the severity of the BPD manifestations and for the CUA utility scores will be derived from the quality of life instrument(s), both with a time horizon of 12 months after the end of treatment. The net benefit will be used to express cost-effectiveness. For each patient, the net benefit will be calculated by subtracting the costs incurred by the patient from the amount that the society is willing to pay for the health benefit [212]. The development of the net benefit over time and differences between the treatments will be modeled using multilevel modeling in which the hierarchical structure of the data and potential missing values are taken into account. The best fitting model to describe the development over time and the appropriate distribution of the net benefit data (e.g., gamma distribution, log-normal distribution) will be based on the data. Cost-effectiveness acceptability curves (CEACs) will be drawn showing the probability that one treatment is more cost-effective compared to the other treatment, given the observed data, for a range of willingness-to-pay values. Sensitivity analyses will be performed to address the uncertainties in methodology and assumptions and to test for the robustness of findings.

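### The stated QALY rule multiplies the change in utility by time rather than its level, so it misstates the health gain in the cost-utility analysis

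*Protocol article*

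**What the plan says.** In the protocol article, under Quality of life, EQ-5D-5L profiles are converted to utilities: "The profiles from the five health state dimensions are assigned a value based on the Dutch social tariffs to generate health utilities". The same paragraph then gives the rule for the cost-utility outcome: "calculate Quality Adjusted Life Years (QALYs) by multiplying the change in utility values between assessments by the length of the period between assessments".

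The schedule is set in two places. Secondary outcome measures: "The outcome measures are administered at baseline and every six months after start of the treatment phase". Procedure and assessments: "patients are reassessed every six months during the two years of treatment", after which "two follow-up assessments (six and 12 months after end of the treatment) will be administered".

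Under Cost-effectiveness, the cost-utility analysis takes its utilities from the quality-of-life instrument or instruments. It and the cost-effectiveness analysis are set "both with a time horizon of 12 months after the end of treatment". Each patient's net benefit is found by "subtracting the costs incurred by the patient from the amount that the society is willing to pay for the health benefit", and its course over time is then modelled. No other section describes an area under the utility curve or modifies the QALY sentence.

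**The concern.** QALYs accumulate as utility level × duration. The stated rule uses the difference between two adjacent utilities in place of the level. Two consequences follow whatever the data look like: a stable patient accrues nothing, whether stable at a good or a poor level, and a patient who improves and stays improved is credited only in the interval in which the change occurs.

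This matters because cost-effectiveness is one of the trial's four primary objectives and the cost-utility analysis is one of its two economic analyses. The arms also differ in timing: under Format, the treatment phase lasts at most 12 months in DBT and 18 months in ST, so the utility courses could plausibly differ in when gains appear. In addition, the cost interview records all resource use since the previous assessment (Costs). Net benefit would then set the full cost of each interval against a health effect that counts only change within it. Treatment selection also lists cost-effectiveness among the outcomes for its generalization analyses.

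**Working it through.** The article gives no QALY figure, so there is none to reproduce. The check compares the stated rule with the standard one.

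**Inputs from the article.** Assessments at baseline and at 6, 12, 18 and 24 months, then 6 and 12 months after treatment (about months 30 and 36); nominal interval L = 0.5 year; horizon T of about 3 years.

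**Assumed, not in the article.** Baseline utility 0.5, improved utility 0.7, and the shapes of the paths below.

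**Formulas**, with u_j the utility at assessment j:
- As written, summed over intervals: Σ (u_{j+1} − u_j) × L_j. With equal L this telescopes to L × (u_last − u_baseline) = 0.5 × (u_last − u_baseline).
- Area under the curve (AUC): Σ [(u_j + u_{j+1})/2] × L_j. Gain = AUC − u_baseline × T.

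**Worked case, rise by month 6 and held.** AUC = 0.6 × 0.5 + 5 × (0.7 × 0.5) = 0.30 + 1.75 = 2.05. Gain = 2.05 − 0.5 × 3 = 0.55. As written: 0.5 × (0.7 − 0.5) = 0.10.

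| Path | AUC | AUC gain | As written | Share of gain |
|---|---|---|---|---|
| Rise by month 6, held | 2.05 | 0.55 | 0.10 | 18% |
| Linear to month 36 | 1.80 | 0.30 | 0.10 | 33% |
| Rise by month 30, held | 1.65 | 0.15 | 0.10 | 67% |
| Rise in last interval only | 1.55 | 0.05 | 0.10 | 200% |
| Rise by month 6, held to 30, lost by 36 | 2.00 | 0.50 | 0.00 | 0% |
| Constant 0.5 | 1.50 | 0 | 0 | – |
| Constant 0.8 | 2.40 | 0 | 0 | – |

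The shares do not depend on 0.5 and 0.7, since both quantities scale with the size of the change. They depend on the path and on the interval lengths.

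**Effect on a comparison.** Suppose one arm followed the early path and the other the linear path to the same endpoint. The AUC difference is 0.55 − 0.30 = 0.25 QALY; the written rule gives 0.10 − 0.10 = 0. Incremental net benefit would be off by 0.25 × the willingness to pay per QALY.

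**Unequal first interval.** Baseline precedes randomization, patients may wait for a slot, and a pretreatment phase of about four weeks comes before the treatment phase from which later assessments are timed. The first interval is therefore at least about 7 months (1 + 6), or 13 months with a six-month wait (6 + 1 + 6). For the early path:
- 7 months (0.58 year): as written 0.2 × 0.58 = 0.116 against an AUC gain of 0.558, a share of 21%.
- 13 months (1.08 years): as written 0.2 × 1.08 = 0.216 against 0.608, a share of 36%.

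Timing now enters, but only as an artefact: the same rise of 0.2 counts 0.216 if it falls in a 13-month interval and 0.100 if it falls in a six-month one.

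**The case against.** Four points can be made for the plan.

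1. *The wording may be shorthand.* Read as change from baseline × interval length, it gives 0.60 for the early path and 0.35 for the linear one, against AUC gains of 0.55 and 0.30. That is close to a proper incremental QALY. But the sentence speaks of change between assessments, and an analyst following it would not compute this. That it can be read two ways is itself a reason to rewrite it.

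2. *The article does not say that the products are summed.* Net benefit over time is to be modelled with multilevel methods, so intermediate values could inform the modelled course. This stands: a reader might infer that the arms would be compared only on last minus baseline utility, but that holds only if products are summed over equal intervals. It does not rescue the rule, because in a repeated-measures model an interval of maintained improvement would still carry a health effect of zero.

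3. *The analyses are declared to be under development.* Statistical analyses calls the methods that follow it examples and promises a published update before data analysis. The QALY sentence, however, stands in the measures part of the article as a plain definition, outside those examples. The promised update offers a convenient place for the correction; it does not make the sentence right. Nor is this a detail left to an analysis plan: the article gives a rule, and the rule is wrong.

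4. *The magnitudes are hypothetical.* They are; the utilities and paths are assumptions. That stable utility scores zero and maintained improvement earns nothing does not depend on them.

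A reader might also infer that the rule discards nearly all of the health gain. The calculations do not support that as a general statement: the share retained runs from 0% to 200% by path, and a gain confined to the last interval is doubled.

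**Conclusion.** The definition is wrong as written and should be corrected before the cost-utility analysis is run. It misstates the health gain in either direction depending on the utility path: for the assumed rise of 0.2, 0.10 in place of 0.55, 0.30 or 0.05, and 0.00 in place of 0.50 for a gain later lost. These sizes rest on assumed utilities and paths, on summing the products, and on nominal six-month intervals; a longer and variable first interval changes the figures without repairing the rule.

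The reach is limited to the cost-utility analysis (net benefit and acceptability curves per QALY) and to analyses that draw on it. It would be going too far to conclude that the whole economic evaluation fails: the cost-effectiveness analysis uses BPD severity. The BPDSI-5 primary outcome and the sample size are likewise untouched.

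**What to change.** In the protocol update promised before data analysis, replace the sentence by a definition such as: QALYs are the sum over intervals of [(utility at start + utility at end)/2] × actual interval length in years, that is, the trapezoidal area under the utility curve over the stated horizon. Apply the same rule to the MHQoL-7D if it is used. Use actual dates, since the time from baseline to the first assessment in treatment varies between patients.

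State also that arms are compared with adjustment for baseline utility. The area under the curve carries the baseline level with it, so a chance imbalance at baseline would otherwise appear as a QALY difference.

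The cost is one or two sentences. Baseline and six-monthly utilities are already collected, so no assessment, sample-size or data-collection change is needed.
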